# Maternal vitamin D supplementation during pregnancy and lactation to promote infant growth in Dhaka, Bangladesh (MDIG trial): study protocol for a randomized controlled trial

**DOI:** 10.1186/s13063-015-0825-8

**Published:** 2015-07-14

**Keywords:** Bangladesh, Lactation, Length, Linear growth, Nutrition, Pregnancy, Stunting, Vitamin D

## Abstract

**Background:**

Vitamin D regulates bone mineral metabolism and skeletal development. Some observational studies have suggested that prenatal vitamin D deficiency increases the risk of adverse pregnancy and/or birth outcomes; however, there is scant evidence from controlled trials, leading the World Health Organization to advise against routine vitamin D supplementation in pregnancy. Importantly, little is known about the effect of maternal vitamin D status on infant linear growth in communities in South Asia where stunting is highly prevalent and maternal-infant vitamin D status is commonly suboptimal.

**Methods/Design:**

The Maternal Vitamin D for Infant Growth study is a randomized, placebo-controlled, dose-ranging trial of maternal vitamin D supplementation during pregnancy and lactation in Dhaka, Bangladesh. The primary aims are to estimate (1) the effect of maternal prenatal oral vitamin D_3_ supplementation (4200 IU/wk, 16,800 IU/wk, or 28,000 IU/wk, administered as weekly doses) versus placebo on infant length at 1 year of age and (2) the effect of maternal postpartum oral vitamin D_3_ supplementation (28,000 IU/wk) versus placebo on length at 1 year of age among infants born to women who received vitamin D 28,000 IU/wk during pregnancy. Generally healthy pregnant women (n = 1300) in the second trimester (17–24 weeks of gestation) are randomized to one of five parallel arms: placebo 4200 IU/wk, 16,800 IU/wk, or 28,000 IU/wk in the prenatal period and placebo in the postpartum period or 28,000 IU/wk in the prenatal period and 28,000 IU/wk in the postpartum period. Household- and clinic-based follow-up of mother-infant pairs is conducted weekly by trained personnel until 26 weeks postpartum and every 3 months thereafter. The primary trial outcome measure is length for age z-score at 1 year of age. Anthropometric measurements, clinical information, and biological specimens collected at scheduled intervals will enable the assessment of a range of maternal, perinatal, and infant outcomes.

**Discussion:**

The role of vitamin D in maternal and infant health remains unresolved. This trial is expected to contribute unique insights into the effects of improving maternal-infant vitamin D status in a low-income setting where stunting and adverse perinatal outcomes represent significant public health burdens.

**Trial registration:**

ClinicalTrials.gov identifier: NCT01924013. Registered on 13 August 2013

**Electronic supplementary material:**

The online version of this article (doi:10.1186/s13063-015-0825-8) contains supplementary material, which is available to authorized users.

## Background

Many low-income countries in Asia have experienced substantial recent reductions in mortality rates among children younger than 5 years of age [1]; for example, Bangladesh has met United Nations Millennium Development Goal 4—a two-thirds reduction in child mortality between 1990 and 2015. However, childhood undernutrition remains a persistent global public health problem [2], particularly in Sub-Saharan Africa and South Asia [3]. In Bangladesh, stunting (height or length less than 2 standard deviations below the standard median for age and sex) was estimated to affect 51 % of children younger than 5 years of age in 2004, but declined to 43 % in 2007 and to 41 % in 2011 according to national surveys [4].

Fetal and early childhood growth is believed to have a critical influence on early childhood infectious disease susceptibility, mortality, and long-term functional and social outcomes, particularly during the first 1000 days of pre- and postnatal development [5, 6]. Postnatal linear growth faltering—an abnormally slow velocity of length/height gain that may eventually lead to stunting—often begins early in infancy in low-income settings (i.e., within the first 3 months of life [7]), suggesting an important contribution by prenatal determinants, including epigenetic and endocrine factors that regulate growth in the first months of life. However, the causal pathways implicated in early childhood stunting remain poorly understood [8, 9].

Vitamin D is a well-established regulator of bone mineral metabolism and skeletal development [10]. Children with severe vitamin D deficiency rickets have secondary hyperparathyroidism and demineralization of the growing skeleton, as well as impairment of bone elongation [11]. Vitamin D treatment of affected children leads to an acceleration of linear growth accompanied by resolution of the hyperparathyroidism [11–13]. Effects of improvements in vitamin D status on linear growth in infants and children without rickets have not been widely studied; however, in one trial in India, weekly vitamin D supplementation of low birth weight infants reduced the risk of stunting in adjusted analyses [14]. Vitamin D status is therefore a logical candidate as a modifiable nutritional determinant of linear growth in communities where stunting is prevalent and vitamin D status is commonly suboptimal. In South Asia, there is a high prevalence of biochemical vitamin D deficiency among women and young infants [15]; in Dhaka, we found that 34 % of pregnant women at 26–29 weeks gestation (*N* = 160) had serum 25-hydroxyvitamin D (25(OH)D) concentrations less than 30 nmol/L, and that 64 % had 25(OH)D levels less than 50 nmol/L [16], a threshold for sufficiency adopted by the Institute of Medicine (IOM) [17]. In the absence of maternal vitamin D supplementation, postnatal infant 25(OH)D concentration was low in the neonatal period, but gradually increased over the first several months of life (unpublished observations). Therefore, in Bangladesh, we have observed that the period of greatest vulnerability with respect to perinatal vitamin D deficiency overlaps with a critical period of fetal and early infant growth. Because maternal vitamin D status is the predominant determinant of fetal and neonatal vitamin D stores [18], prenatal vitamin D supplementation represents the optimal approach to testing the effect of improving maternal-infant vitamin D status on fetal-infant growth and other health outcomes.

Observational studies of the association between maternal prenatal vitamin D status and infant anthropometry have yielded conflicting findings [19–23]. The effects of prenatal vitamin D supplementation on infant length have not been widely studied in controlled trials. In a study conducted in the 1970s in London, England, prenatal vitamin D supplementation reduced the risk of small for gestational age (SGA) versus control, but there was no significant effect on birth length [24]; however, the infants in the vitamin D group had significantly greater mean length at 1 year of age [25]. We recently completed a randomized, placebo-controlled, double-blinded trial of maternal third-trimester vitamin D_3_ supplementation in Dhaka, in which 160 women were randomized to receive either 35,000 IU/wk or placebo until delivery. Maternal mean 25(OH)D was significantly higher at delivery after receiving vitamin D versus placebo (134 vs. 39 nmol/L; *P* < 0.001; *N* = 133). There was a parallel difference in cord 25(OH)D (103 nmol/L in vitamin D group vs. 39 nmol/L in placebo group; *P* < 0.001; *N* = 132) [16]. Analyses of the effect of prenatal vitamin D supplementation on infant length among 134 infants followed up to 1 year of age revealed that infants born to women in the vitamin D group had mean length for age z-scores (LAZs) at 1 year that were significantly greater than infants in the placebo group (mean = 0.44 z-score units higher; 95% confidence interval [CI], 0.06–0.82) [26]. This corresponded to an approximate halving of the prevalence of stunting (11 % vs. 21 %), which would constitute a substantial public health benefit. The effect appeared to be attributable to a significantly accelerated increase in mean LAZ from birth to 1 month of age (change of 0.53 z-score in vitamin D versus 0.19 z-score in placebo group; *P* = 0.004) rather than a significant difference in birth length [26]. However, some animal [27] and observational [21, 28] studies have suggested an effect of maternal prenatal vitamin D status on growth of the fetus.

There has been considerable recent interest in the role of vitamin D in maternal and infant health outcomes in low-income settings [29]. Some observational studies have suggested that antenatal vitamin D deficiency increases the risk of adverse pregnancy and birth outcomes, including SGA [30, 31]. However, there is scant evidence from controlled clinical trials [31, 32], and the World Health Organization (WHO) recently advised against routine vitamin D supplementation in pregnancy until further data become available [33]. Building on our earlier findings of a beneficial effect of prenatal vitamin D supplementation on infant length in a preliminary trial [26], we are conducting a larger dose-ranging trial of maternal vitamin D_3_ supplementation in Dhaka, Bangladesh. The primary aim is to investigate the effect of maternal vitamin D supplementation on infant length at 1 year of age, but the trial also provides an opportunity to study a range of other potential vitamin D–responsive outcomes.

## Methods/Design

The Maternal Vitamin D for Infant Growth (MDIG) trial is randomized, placebo-controlled, dose-ranging trial of maternal vitamin D supplementation during pregnancy and lactation to improve infant linear growth in Dhaka, Bangladesh (ClinicalTrials.gov identifier NCT01924013). A detailed trial protocol was developed in accordance with the SPIRIT guidelines [34] through a collaboration between the International Centre for Diarrhoeal Disease Research (ICDDR,B; Dhaka, Bangladesh) and the Hospital for Sick Children (Toronto, ON, Canada) and with funding from the Bill and Melinda Gates Foundation through its Achieving Healthy Growth platform (http://gcgh.grandchallenges.org/grantopportunities/pages/healthygrowth.aspx).

The first participant was enrolled on 18 March 2014; enrollment is expected to proceed until August 2015; and planned data collection will continue until 2018.

### Objectives

The primary aims of the trial are to estimate (1) the effect of maternal prenatal oral vitamin _D3_ supplementation (4200 IU/wk, 16,800 IU/wk, or 28,000 IU/wk administered as weekly doses) versus placebo on infant length at 1 year of age in Dhaka, Bangladesh; and (2) the effect of maternal postpartum oral vitamin D_3_ supplementation (28,000 IU/wk) versus placebo on length at 1 year of age among infants born to women who received vitamin D 28,000 IU/wk during pregnancy. Secondary anthropometric outcomes include birth size and the prevalence of SGA, the prevalence of stunting at 1 year of age, and mean attained LAZ and stunting prevalence at 2 years of age.

Clinical, biochemical, and microbiological surveillance of enrolled mother-infant pairs will enable a range of secondary objectives to be addressed, including (1) estimation of the effect of maternal vitamin D supplementation on the incidence of acute respiratory infections (ARIs) during early infancy; (2) exploration of the roles of specific hormones, nutrients, environmental contaminants, and inflammatory markers in the mediation or modification of the effect of vitamin D on fetal and infant growth, with particular emphasis on the role of the parathyroid hormone (PTH) system; and (3) investigation of the role of epigenetic modification of genes involved in perinatal vitamin D metabolism in infant stunting.

### Setting and participants

Recruitment, enrollment, and clinical activities are based at the Maternal and Child Health Training Institute (MCHTI), a Bangladeshi national government-operated facility that provides health care to pregnant women and children in its referral area in central Dhaka, Bangladesh. MCHTI has outpatient antenatal care clinics, a labor and delivery unit, and inpatient pediatric services. The Dhaka wards and/or unions near MCHTI that are included in the trial area include Kamrangirchar, Azimpur, Lalbag, and Hazaribag. About three-fourths of the participants are expected to be residents of Kamrangirchar, a group of urban slums on the Buriganga River along the periphery of Dhaka city. The area is densely populated, with a total population of about 300,000, of whom approximately 265,000 reside in slum settlements [35]. The literacy rate is approximately 29 % (compared with the national average of 32 %) and more than 30 % of the residents have monthly incomes of 5000 taka (about US$60) or less. Income earners are mainly day laborers (e.g., rickshaw pullers), and many men work in local tanneries or operate small businesses. However, the socioeconomic status of residents varies, owing to the presence of some universities and government offices in the area.

The MDIG trial is an efficacy study designed to test a specific biological mechanism implicated in fetal and infant growth. We therefore established a detailed set of eligibility criteria that will optimize the internal validity of the trial by minimizing the number of withdrawals due to loss to follow-up or serious adverse events, acknowledging that this may theoretically reduce the generalizability of the findings. Among women presenting to MCHTI for antenatal care, participant eligibility is based on the following inclusion criteria: age 18 years and older, intention to reside in the trial area for at least 18 months, and currently at 17–24 completed weeks of gestation (i.e., 17 weeks + 0 days to 24 weeks + 0 days, inclusive) based on recalled last menstrual period (LMP) and ultrasound performed by MCHTI technicians (Just Vision 400, Toshiba, Tokyo, Japan; SonoAce X8, Samsung Medison, South Korea). All potential participants undergo routine ultrasound. If there is a difference of more than 10 days between gestational age (GA) calculated using the recalled LMP and second-trimester ultrasound, the estimated date of delivery is adjusted as per the second-trimester ultrasound. Otherwise, the GA date based on recalled LMP is used [36]. If more than one ultrasound report is available, GA estimation is based on the earliest of the ultrasounds. If the earliest ultrasound was performed in the first trimester and there is a difference of more than 5 days between GA calculated using the recalled LMP and first-trimester ultrasound, the estimated date of delivery is adjusted as per the first-trimester ultrasound [36].

Pregnant women are not enrolled if any of the following exclusion criteria apply: self-reported history of any medical condition or medications that may predispose to vitamin D sensitivity, altered vitamin D metabolism, and/or hypercalcemia (e.g., active tuberculosis or current therapy for tuberculosis, sarcoidosis, history of renal and/or ureteral stones, parathyroid disease, renal or liver failure, or current use of antiseizure medications); high-risk pregnancy based on point-of-care (POC) testing (hemoglobin [Hb] <70 g/L; proteinuria, defined as ≥300 mg/dl based on urine dipstick; hypertension, defined as systolic blood pressure ≥140 mmHg and/or diastolic blood pressure ≥90 mmHg); high-risk pregnancy based on maternal report and/or past ultrasound findings (multiple gestation, major congenital anomaly, severe oligohydramnios); unwillingness to stop taking non-study vitamin D or calcium supplements or a multivitamins containing calcium and/or vitamin D; currently prescribed vitamin D supplements as part of a physician’s treatment plan for vitamin D deficiency; and/or previous enrollment in the MDIG trial during a prior pregnancy.

All participants provide written informed consent before randomization. The informed consent process is undertaken in conjunction with the iterative eligibility assessment: preliminary screening (based on age, location of residence, plans to remain in referral area), detailed medical screening by a study physician, POC testing (blood pressure, urine dip, Hb), and obstetric ultrasound. Women may choose to exit the enrollment process at any time. Among prospective participants who complete the screening process and are found to meet all criteria, a detailed discussion of the trial is undertaken before written informed consent is sought. Eligible pregnant women are encouraged to discuss trial participation with their spouse and/or other family members before finalizing consent. Two additional consent procedures are undertaken at a later time for supplemental study procedures: (1) husbands of enrolled participants are approached to obtain consent for paternal anthropometry and blood specimen collection, and (2) enrolled participants are approached at or beyond 30 weeks of gestation to request the participation of their infant in an ARI substudy during the 0- to 6-month postnatal period (detailed methods of the ARI substudy will be presented elsewhere).

### Design and sample size

The MDIG trial is a randomized, placebo-controlled, double-blinded, dose-ranging trial with a 1:1 allocation ratio across five parallel groups (Fig. 1). A total of 1300 pregnant women will be randomized, with a target of allocating 260 women in each group (Fig. 1). The primary outcome analysis will be a between-group comparison of mean LAZs at 1 year of age, assuming up to 15 % attrition from each group before this time point. To assess the effect of prenatal vitamin D, we plan to perform five primary between-group analyses, comprising each vitamin D dose versus placebo (three comparisons) and comparisons between adjacent doses (two comparisons). A conservative approach to addressing multiple testing is to partition the α (risk of type I error) among the five comparisons (conventional overall 0.05 divided by 5); thus, each between-group comparison will be tested as a two-sided test with an α of 0.01, assuming 90 % power. With 220 analyzable participants per group (about 85 % of total enrolled), the minimum detectable difference in LAZ will be 0.40 z-score units, which equates to approximately 1.0 cm at 1 year of age based on WHO growth standards. In our preliminary trial, we observed an increase in LAZ of 0.44 at 1 year attributable to prenatal vitamin D supplementation, which corresponded to an increase of 1.1 cm (95 % CI, 0.06–2.0), adjusted for sex [26].

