**Fig. 1 Fig1:**
[figure not shown]
Maternal Vitamin D for Infant Growth (MDIG) trial flow diagram. The allocated intervention in each group is shown as “prenatal intervention; postpartum intervention”

The secondary analysis at 2 years of age will enable detection of an approximately 1.2-cm difference between groups. For the postpartum effect analysis of 28,000 IU/wk versus placebo postpartum among women who received 28,000 IU/wk antenatally, the comparison at 1 year of age will have a minimum detectable difference of 0.31 z-score units (assuming 90 % power, a 5 % risk of a type I error for a two-sided test, and at least 220 participants per group). Based on WHO growth standards, this is approximately 0.77 cm at 1 year of age and 0.96 cm at 2 years of age. Because the α is not subject to multiple testing for the postpartum effect analysis, there is greater precision to detect a smaller difference compared with the prenatal effect analysis. In order to enroll 1300 participants, we expect to provisionally screen approximately 15,000 pregnant women for eligibility. The major reasons for exclusion during preliminary screening are GA beyond 24 weeks and residence outside the study area.

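### The two stated minimum detectable differences, 0.40 at α 0.01 and 0.31 at α 0.05, cannot both hold at 220 per group, 90% power and one SD

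*Protocol article*

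**What the plan says.** All of this is in the protocol article, section Design and sample size, unless noted.

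- Prenatal comparisons: the α comes from a decision to "partition the α (risk of type I error) among the five comparisons (conventional overall 0.05 divided by 5"), so that "each between-group comparison will be tested as a two-sided test with an α of 0.01, assuming 90 % power". The sample is given as "With 220 analyzable participants per group (about 85 % of total enrolled"), and the result as "the minimum detectable difference in LAZ will be 0.40 z-score units", put at about 1.0 cm at 1 year. The corresponding 2-year figure is about 1.2 cm.
- Postpartum comparison (paragraph after the Fig. 1 caption): "the comparison at 1 year of age will have a minimum detectable difference of 0.31 z-score units", with 90% power, a two-sided 5% type I error and "at least 220 participants per group". This is put at about 0.77 cm at 1 year and 0.96 cm at 2 years.
- The same paragraph explains the smaller postpartum figure by the absence of a multiplicity adjustment and gives no other reason.
- The Statistical analysis section describes each prenatal comparison as in effect an independent-samples t test and says the postpartum comparison uses a similar approach.
- Neither figure is accompanied by an SD. The Background section reports the preliminary trial's difference at 1 year among 134 infants ("mean = 0.44 z-score units higher", 95% CI 0.06 to 0.82).

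**The concern.** The two figures share the outcome, the age, the power, the sidedness, the 1:1 allocation and the number per group. By the article's own account they differ only in α. A change of α from 0.05 to 0.01 raises the minimum detectable difference by a known factor that does not depend on the SD, and the printed pair does not show that factor.

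Both comparisons are primary aims. The stated figures tell a reader what a null result could rule out. If the postpartum figure is the wrong one, the trial has less than the stated 90% power at 0.31, and a null postpartum result would be read as more informative than it is. If the prenatal figure is the wrong one, the article understates what the trial can detect.

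**Working it through.** **Inputs.** n = 220 per group, power 90%, two-sided tests, α = 0.01 (prenatal, 0.05/5) and α = 0.05 (postpartum), all from Design and sample size. The test is a two-sample comparison of means (Statistical analysis). The SD is not given and is treated as unknown.

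**Formula.** By the normal approximation, MDD = SD × (z₁₋α/₂ + z₀.₉₀) × √(2/n). The noncentral t gives nearly the same values and is used below.

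**Step 1: reproduce the figures in SD units at n = 220.**
- α = 0.05: (1.960 + 1.282) × √(2/220) = 0.309 (t: 0.310). With SD = 1.00 this reproduces the stated 0.31.
- α = 0.01: (2.576 + 1.282) × √(2/220) = 0.368 (t: 0.369). With SD = 1.00 this gives 0.37, not the stated 0.40.

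**Step 2: compare ratios, where the SD cancels.**
- Required: 3.858/3.242 = 1.190 (t: 0.3692/0.3097 = 1.192).
- Stated: 0.40/0.31 = 1.290.
- Widest range that rounding allows: 0.395/0.315 = 1.254 to 0.405/0.305 = 1.328. The required 1.19 lies outside it.

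**Step 3: find the SD each figure needs.**
- 0.40: 0.40/0.3692 = 1.083 (1.070 to 1.097 with rounding).
- 0.31: 0.31/0.3097 = 1.001 (0.985 to 1.017 with rounding).
- The ranges do not overlap.

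**Step 4: try to rescue the pair.**
- More than 220 in the postpartum comparison: with SD 1.083, 0.31 needs about 258 per group. Only 260 are randomized per group and up to 15% loss is assumed (260 × 0.85 = 221).
- Other inputs for the 0.40 figure at SD 1.00 and 220 per group (normal approximation): one-sided 0.344; 80% power 0.326; α = 0.005 0.390; α = 0.05/6 0.374; pooling the two prenatal 28,000 IU/wk groups (440 v 220) 0.319. None gives 0.40.
- 0.40 does appear with 95% power (0.402) or with 187 analyzable per group (0.399). Both contradict the text.

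**Step 5: the two possible readings.** The article's own conversions are about 2.5 cm per z at 1 year (1.0/0.40; 0.77/0.31 = 2.48) and 3.0 to 3.1 cm per z at 2 years (1.2/0.40; 0.96/0.31).

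| | SD 1.00 | SD 1.083 |
|---|---|---|
| Prenatal MDD, α 0.01 | 0.37 (stated 0.40) | 0.40 |
| Postpartum MDD, α 0.05 | 0.31 | 0.34 (stated 0.31) |
| Power at the stated 0.40 | about 95% | 90% |
| Power at the stated 0.31 | 90% | about 85% |
| Figures in cm that change, 1 year | 1.0 becomes about 0.92 | 0.77 becomes about 0.83 |
| Figures in cm that change, 2 years | 1.2 becomes about 1.1 | 0.96 becomes about 1.04 |

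**Step 6: what the preliminary trial suggests.** The half-width is (0.82 − 0.06)/2 = 0.38, so SE = 0.38/1.978 = 0.192. If the estimate is unadjusted and the 134 infants split 67/67, SD = 0.192/√(2/67) = 1.11. With 134 infants, the 95% interval around that SD is about 0.99 to 1.26, which includes 1.00.

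**The case against.** The best defence accepts the arithmetic and disputes its weight. With SD 1.00, the 0.31 figure and its 0.77 cm are right. Only 0.40 is off, and in the safe direction, so no comparison is underpowered. The prenatal tests will use the Holm procedure, which is never less powerful than testing each comparison at 0.01. In the less favourable reading, the postpartum figure moves by about 0.03 z, or 0.06 cm, which is less than the 0.1 cm unit in which length is recorded. Both printed figures lie below the 0.44 seen in the preliminary trial, and neither is presented as a target effect. All of this stands, and it limits the seriousness. It does not remove the contradiction.

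A reader might infer from the preliminary interval that the postpartum figure is the wrong one and that this comparison is underpowered. The document does not support that conclusion. The SD of about 1.1 is a back-calculation that assumes an unadjusted, near-even comparison. The Background does not say how the interval was modelled, and the related length difference in centimetres is described as adjusted for sex. The preliminary stunting prevalences (11% v 21%) with the 0.44 difference imply an SD of about 1.05 under normality and equal SDs, with a range of 0.95 to 1.17 from rounding alone. The evidence leans toward an SD above 1 but does not exclude 1.00.

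The absence of a stated SD is not itself a finding. An article condenses the full protocol, and the SD may be given there. The point rests only on two printed figures that disagree.

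**Conclusion.** The pair 0.40 and 0.31 is inconsistent as written, so at least one power statement for a primary aim is wrong. This rests on the same n, power, sidedness and SD applying to both figures. The article states the first three, and it supports the common SD by using the same outcome and age and by naming α as the only reason for the difference.

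The size is modest. Either the prenatal figure should be 0.37 (a conservative error), or the postpartum figure should be 0.34, with power at 0.31 of about 85% in place of 90%. Which applies depends on the SD that was assumed, and the document does not settle it. The point calls for correcting a stated figure. It does not put the sample size, the tests or the α levels in question.

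**What to change.** State the single SD of LAZ at 1 year that the calculation assumes, recompute both minimum detectable differences from it at 220 per group, and update the centimetre values that depend on the figure that changes.

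- With SD 1.00: 0.37 (prenatal) and 0.31 (postpartum). The prenatal centimetre values become about 0.92 at 1 year and 1.1 at 2 years; 0.77 and 0.96 stay.
- With SD about 1.08: 0.40 and 0.34. The postpartum values become about 0.83 cm and 1.04 cm; 1.0 and 1.2 stay.
- With another SD, multiply it by 0.369 and 0.310. For example, SD 1.11 gives 0.41 and 0.34.

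If 0.40 came from a different power or number analyzed, state that input instead. The cost is wording only: enrolment stays at 1300, and no test or α changes.
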